**Fig. 1 Fig1:**
[figure not shown]
Of the recruitment and study procedure

### Randomisation

Randomisation will be computerised and be stratified for centre. Block randomisation with varying predefined block sizes is used combined with minimisation. Block randomisation will be dominant over minimisation. The randomisation will be minimised taking account of: a) use of medication for ADHD (medication versus no medication); b) past participation in a psycho-education training (psycho-education versus no psycho-education); c) gender (male versus female); and d) subtype ADHD (combined, hyperactive-impulsive, inattentive and not otherwise specified). The researcher will be blind for the block sizes.

### Blinding

Blinded assessments by a psychiatrist or specialist nurse with the investigator-rated screening version of the Conners’ Adult ADHD Rating Scale (CAARS-INV) will take place at baseline and 3, 6 and 9 months after baseline. At baseline patient nor interviewer will know in which group the patient will be placed. To ensure that the interviewers stay blind during the other time points of assessment, patients will be instructed at the research interview not to share information about allocation with the interviewer. At the beginning of each assessment, the interviewer will repeat this instruction.

### Outcome measures

#### Selection and diagnostic measures

The Diagnostic Interview for ADHD in adults (DIVA) [32] is a structured interview used in our study to diagnose ADHD in adults. The first part consists of the DSM-IV criteria of ADHD in childhood and adulthood and the second part is to determine impairment in five domains (education and work, relationships and family life, social contacts, leisure time and self-confidence) in both life periods. Whenever possible, the information provided by the patient is supplemented by collateral information from a family member or partner and by school reports.

#### Primary outcome measure

##### ADHD symptoms (investigator-rated)

We will use the investigator-rated screening version of the Conners’ Adult ADHD Rating Scale (CAARS-INV: SV) [35] by a blinded clinician to assess DSM-IV criteria symptoms as well as specific manifestations of ADHD, such as mood lability. This interview consists of 30 items, which are rated on a 4-point Likert scale. Ratings can be organised in three subscales: Inattention, Hyperactivity/Impulsivity, and the ADHD index. All subscales have shown good internal consistency and inter-rater reliability, as well as sensitivity to treatment outcome [36]. Cronbach’s α coefficients vary from .74 to .94 and intraclass correlations between investigator-ratings and self-ratings ranged from .45 to .87 [36].

#### Secondary outcome measures

##### ADHD symptoms (self-reported)

The self-report version of the Conners’ Adult ADHD Rating Scale (CAARS-S:SV) [35] will be used to assess self-reported ADHD symptoms. This questionnaire consists of 30 items, which are rated on a 4-point Likert scale, and has the same structure as the investigator version. The internal consistency is comparable with that of the investigator version and Cronbach’s α coefficients vary from .76 to .95 at different time points [36].

##### Executive functioning

The self-report version for adults of the Behaviour Rating Inventory of Executive Function (BRIEF-A) [37] will be used to measure executive functioning in daily life. This questionnaire consists of 75 items on a 3-point Likert scale and has nine subscales: Inhibit, Shift, Emotional Control, Self-monitor, Initiate, Working Memory, Plan/Organise, Task Monitor, and Organization of Materials. Three validity scales are included: Negativity, Infrequency, and Inconsistency. For the Dutch version of the BRIEF-A internal consistency varies with Cronbach’s α coefficients ranging from .70 to .89 and test-retest reliability was found to be .70 or higher [38].

##### Mindfulness skills

We will use the short form of the Five Facet Mindfulness Questionnaire (FFMQ-SF) [39, 40] to measure mindfulness skills. This self-report questionnaire consists of 24 items which are rated on a 5-point Likert scale. Five facets of mindfulness are distinguished: Observing, Describing, Acting with Awareness, Non-judging, and Non-reactivity. The Dutch version of the FFMQ-SF has been shown to be a reliable instrument which is sensitive to change in a population with depressive and anxiety symptoms. Cronbach’s α coefficients between .75 and .87 have been found [39].

##### Self-compassion

The short form of the Self-Compassion Scale (SCS-SF) [41, 42] will be used to measure self-compassion. This instrument consists of 12 item based on a 7-point Likert scale and measures six components of self-compassion: Self-kindness, Self-judgement, Common Humanity, Isolation, Mindfulness and Over-identification. The shortened scale shows a near-perfect correlation with the original Self-Compassion Scale. In a Dutch population, Cronbach’s α coefficient for the full scale is .87 and the coefficients for the subscales of the SCS-SF vary from .55 to .81. The internal consistency of one of the components (Self-kindness) was relatively low [41].

##### Positive mental health

The short version of the Mental Health Continuum (MHC-SF) will be used to measure positive mental health [43, 44]. This self-report questionnaire has 14 items which are scored on a 6-point Likert scale and three subscales: Emotional, Psychological and Social. The Dutch version of this instrument has a good internal reliability with Cronbach’s α coefficients varying between .74 and .89 [43].

##### General functioning

We will use the Outcome Questionnaire (OQ 45.2) [45] to measure general functioning. This self-report questionnaire consists of 45 items and three subscales: Symptom Distress, Interpersonal Relations, and Social Role. The items are scored on a 5-point Likert scale. Cronbach’s α coefficients ranged from .70 to .93 and test-retest reliability with Pearson’s *r* varied from .78 to .84 [45]. The Dutch version of the OQ has comparable psychometric properties with Cronbach’s α coefficients between .69 and .93 and Pearson’s *r* from .70 to .83 in a clinical population [46].

#### Cost-effectiveness

##### Resource use

Resource use will be collected and calculated with the latest version of the Trimbos/iMTA questionnaire for costs associated with psychiatric illness (TiC-P) [47]. This self-report instrument consists of two parts: a) healthcare consumption including contacts within the mental and the general healthcare sector and the use of medication; b) productivity loss. The recall period for the TiC-P is three months for healthcare consumption and one month for productivity loss. Test-retest reliability is satisfactory to almost perfect for most items related to healthcare consumption and satisfactory for items on absence from work and presenteeism. Cohen’s kappa values range from .49 to .84 [48].

##### Quality Adjusted Life Years (QALYs) health gains

We will use the 12-item Short Form (SF-12) Health Survey [49], a shortened version of the SF-36 [50], which is a widely used instrument for measuring health status to calculate QALYs. The SF-12 is a self-report questionnaire with eight domains divided in two components: a physical component summary (Physical Functioning, Role Limitations due to Physical Problems, Bodily pain, General Health) and a mental component summary (Role Limitations due to Emotional Problems, Mental Health, Social Functioning, Vitality). Acceptable levels of internal consistency have been found, with Cronbach’s α coefficients of .84 for the physical component and .81 for the mental component [51]. Test-retest reliability coefficients of .89 for the physical component and .76 for the mental component have been measured in a US population [49].

#### Process measure

##### Adherence to MBCT

During the nine weeks of participation in the MBCT group, we will assess adherence to mindfulness exercises with a calendar on which patients fill out total minutes of formal (e.g. sitting meditation) and informal practice (e.g. mindful eating) on a daily basis. For patients allocated to the MBCT group, we will assess adherence during 6 and 9 months after baseline by questions in which patients are asked to estimate total minutes of formal and informal practice during an average week in the last three months. To check for compliance with the instruction to refrain from mindfulness training during the nine months of the study, patients in the TAU group will be asked whether they participated in an MBSR or MBCT course during the study at the different time points of assessment.

### Intervention

We developed a protocol primarily based on the Mindfulness-Based Cognitive Therapy (MBCT) for recurrent depression [20]. We made some modifications to make the intervention more suitable for adults with ADHD. For example, the psycho-education sections about depression are replaced by psycho-education about ADHD. We also include elements of the Mindful Awareness Practices for ADHD programme (MAPs) [30]. For example, in accordance with the MAPs protocol: a) the meditation periods are built up more gradually compared to the regular MBCT programme; b) mindful awareness in daily life is emphasized; and c) one session is focused on mindful listening and speaking. Table 1 shows the content of the MBCT programme as it will be used.

**Table 1 Tab1:** Content of MBCT programme for ADHD per session

Theme of the session	Mindfulness exercises	(Psycho-)education	Homework
1. Automatic pilot	- 3-min breathing space	- Rationale of mindfulness for ADHD	- 3-min breathing space
	- Raisin exercise	- Introduction in methods to integrate mindfulness in daily life: Support, Structure and Strategy (3 S’s)	- Attention for a routine activity
	- Bodyscan		- Mindful eating
			- Optional: bodyscan
2. Dealing with barriers	- Bodyscan	- Imagery exercise to demonstrate relationship between thoughts and feelings	- 3-min breathing space
			- Attention for a routine activity
			- Bodyscan
	- Sitting meditation with focus on breath	- Exploration of application of the 3 S’s	- Awareness of pleasant events
	- 3-min breathing space		
3. Mindfulness of the breath	- Sitting meditation with focus on breath, body	- Seeing exercise a) to demonstrate the difference between observation and interpretation, b) to discuss dealing with sensory input	- 3-min breathing space
			- Floor yoga or sitting meditation
	- 3-min breathing space	- Exploration of pleasant events	- Awareness of unpleasant events
	- Floor yoga practices		
	- Walking meditation		
4. Staying present	- Sitting meditation with focus on breath, body, sounds	- Exploration of unpleasant events with attention for the interrelatedness of feelings, thoughts and bodily sensations	- 3-min breathing space
			- Sitting meditation
	- 3-min breathing space	- Exercise focused on recognition and dealing with ADHD core symptoms	- Awareness of top 3 ADHD symptoms
	- Walking meditation		
5. Allowing and letting be	- Sitting meditation with focus on breath, body, sounds, thoughts and feelings	- Reflection on intention of participating	- 3-min breathing space
		- Psycho-education about reacting versus responding in stressful situations and when ADHD symptoms are severe	- Sitting meditation or standing yoga
	- 3-min breathing space ‘coping’		- Awareness of communication difficulties
	- Standing yoga practices		
6. Mindful communication	- Standing yoga practices	- Exercise in mindful listening and speaking	- 3-min breathing space
	- 3-min breathing space	- Non-verbal communication exercise	- Sitting meditation or standing yoga
			- Mindful listening and speaking
Silent day	- Varying meditation exercises		
	- Silent lunch and tea break		
7. Taking care of yourself	- Sitting meditation with focus on breath, body, sounds, thoughts, emotions an choiceless awareness	- Exercise on taking care of yourself by examining how to improve balance in life	- 3-min breathing space
			- Practice without CDs
			- Reflect on training
	- 3-min breathing space		- Making an action plan
8. The rest of your life	- Bodyscan	- Reflection on the training	
	- 3-min breathing space	- Maintaining practice	

The protocol has been tested in three consecutive pilot groups of ADHD patients and has been adapted according to their feedback. The 8-week programme will consist of weekly sessions lasting 2.5 hours, and a silent day between session six and seven. In addition to the group sessions, participants will be instructed to practice six days a week for approximately 30 min a day and complete home practice assignments. The participants will receive a set of CDs containing guided mindfulness exercises for home practice ranging in length from 10 min to 45 min.

#### Mindfulness teachers

The MBCT will be taught by mindfulness teachers meeting the advanced criteria of the Association of Mindfulness Based Teachers in the Netherlands and Flanders and the internationally agreed good practice guidelines of the UK Network for Mindfulness-Based Teachers http://mindfulnessteachersuk.org.uk/pdf/teacher-guidelines-2015.pdf) which include: a) a minimum of 150 h of education in MBSR/MBCT background and theory including a reflection report; b) relevant professional training; c) minimum of three years of practicing meditation regularly and attending retreats; d) having attended MBSR/MBCT as a participant; e) continued training; and f) giving a minimum of two courses per two year. The teachers will receive additional training in the study protocol at the start of the project. We will organise peer supervision meetings every three weeks during the intervention phase of the trial. Intervention integrity consisting of adherence to the original programme, the degree to which the intervention is delivered as intended and teacher competency, will be assessed by the Mindfulness-based Interventions-Teaching Assessment Criteria (MBI: TAC) [52]. Videotapes of a random selection of sessions will be assessed by assessors who are familiar with this mindfulness-based programme, are 'proficient' (level 5) according to the MBI: TAC and have received training in the use of these assessment criteria.

### Sample size

The power calculation has been based on our previous randomised controlled study consisting of 103 adults with ADHD (Hepark et al., submitted) in which we demonstrated a significant difference in post-assessment clinician-rated ADHD symptoms (CAARS-INV) [36] between the MBCT and waitlist control group. Based on these study results, we expect a post-treatment difference of 4 between the two groups with a standard deviation of 7.5. Using a two-sided test with an alpha of 0.05, a power of 80 % and analyzing the data using ANCOVA assuming the correlation between pre- and post-assessments to be 0.5, we would need approximately 45 patients per arm. Taking account for loss of power due to drop out of 25 %, we intend to include 120 patients, 60 patients per group.

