The NICE guideline recommends group Cognitive Behavioural Therapy (CBT) for adults with ADHD whose response to medication is insufficient, who have difficulty adhering to drug treatment or who are not willing to use medication. Some studies have shown evidence for the efficacy of treatment with CBT in adults with ADHD, particularly when combined with medication [16]. For example, Safren et al. [17] found support for the effectiveness of individual CBT for patients with ADHD, who are treated with medication but continue to have residual symptoms, compared to a time-matched comparison treatment. Another study of Solanto et al. [18] showed that meta-cognitive group therapy, which is a cognitive-behavioural intervention, provides significant benefit to patients with ADHD with respect to the severity of ADHD symptoms in comparison with supportive group therapy. However, more controlled research studies are required. Another promising psychosocial intervention for patients with ADHD is Mindfulness-Based Cognitive Therapy (MBCT), which combines methods of CBT and mindfulness meditation. Mindfulness is defined as paying attention in a particular way: on purpose, in the present moment, and non-judgmentally [19]. MBCT is usually offered in a group format, consisting of 8 weekly sessions of 2,5 hours and a silent day [20], which may be more cost-effective than individual treatment. In recent years, mindfulness based therapy, such as MBCT, has been demonstrated to reduce anxiety, depression and stress in a wide range of psychiatric disorders [21], including current anxiety and depressive disorders [22]. Furthermore, there is evidence that mindfulness meditation strengthens attention regulation [23–25] and improves some executive functions [26] in healthy subjects. Although these studies were not focused on patients with ADHD and replication studies need to be carried out, this is promising evidence in the search for an effective non-pharmacological treatment for this patient group.

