### Statistical analyses

#### Primary analyses

Baseline socio-demographic and clinical characteristics of the MBCT group and the TAU group will be compared to check whether these characteristics will have been evenly distributed by randomisation. The primary analyses will be aimed at comparing results on the outcome measures at three months after baseline between the MBCT group and the TAU group, controlling for baseline levels and possible other baseline differences between intervention and control groups (despite randomisation).

The outcome data will be analysed and reported according to the CONSORT guidelines and will include both intention-to-treat analyses and per-protocol analyses with the treatment-adherent sample (patients in the MBCT group have to attend at least four of MBCT sessions and patients in the TAU group do not attend a mindfulness-based programme). Percentages of improved, recovered, unchanged and worsened patients in the intervention and control groups will be provided on the basis of predefined cut-off scores (*T-*score greater than 65) and standard deviations. In addition, a Cohen’s *d*-type effect size will be calculated.

In order to investigate consolidation of treatment effect at 6 and 9 months after baseline, we will study whether there is an intervention by time interaction with a mixed model to accommodate for repeated measures. Such an interaction would imply that long term effects are different from short term effects. In addition, regression models will be used to derive prediction models for therapy outcome.

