## Discussion

Adult ADHD has a substantial personal and economic impact and consequently there is a high need for evidence-based treatments for this patient group. Although pharmacotherapy has shown to be effective in reducing ADHD symptoms and its economic impact, there is a call for psychosocial interventions to offer in addition to pharmacotherapy or as an alternative treatment. At this moment research examining the effectiveness of psychosocial interventions for adult ADHD is still in its infancy. Mindfulness training, such as MBCT, is a promising psychosocial intervention, which can be offered in a group format. Considered from an economic perspective, this is an advantage over treatment on individual basis. Previous studies support the feasibility of mindfulness training for this patient group and provide preliminary, but consistent evidence that this intervention reduces ADHD symptoms and improves executive functioning. However, the methodology of these studies is limited by single-centre enrolment [27–29], and (Hepark et al., submitted) lack of follow-up periods [27–29], and (Hepark et al., submitted) small sample sizes [27–29], lack of a control group [27, 28] and lack of blinded assessments [27–29]. Our study will take account of these limitations and will examine the effectiveness of MBCT in adults with ADHD in further detail.

To our knowledge, this is the first properly powered randomised controlled study in this field, that contains blinded outcome assessments and an intention-to-treat analysis. Besides, a follow-up period with a length of six months after the end of treatment is included to consider potential long-term effects of MBCT. To enhance generalisability, this study is conducted in three different mental health centres with expertise in treating adults with ADHD. Additionally, cost-effectiveness will be assessed to evaluate whether MBCT is a cost-effective intervention compared to the treatment as usual and to examine the financial consequences of implementing this intervention. This trial will offer valuable information on whether MBCT has an effect on clinician-rated and self-reported ADHD symptoms, executive functioning, general functioning, positive mental health, self-compassion and medical and societal costs in comparison to treatment as usual.

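### The sample size makes no allowance for therapy-group clustering in the MBCT arm, and the described primary analysis names no MBCT-group term

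*Protocol article*

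**What the plan says.** The Sample size section of the protocol article fixes every input to the calculation:

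- Test: "Using a two-sided test with an alpha of 0.05, a power of 80" per cent.
- Effect: "we expect a post-treatment difference of 4 between the two groups with a standard deviation of 7.5".
- Model: "analyzing the data using ANCOVA assuming the correlation between pre- and post-assessments to be 0.5".
- Result: "we would need approximately 45 patients per arm".
- Inflation: "Taking account for loss of power due to drop out of 25" per cent, leading to 60 per arm and 120 in all.

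On delivery, the Background says that "MBCT is usually offered in a group format, consisting of 8 weekly sessions of 2,5 hours and a silent day". That describes MBCT in general. The Intervention section confirms it for this trial: weekly sessions, referred to as group sessions, with home practice in addition. The comparator is TAU alone.

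On analysis, the Primary analyses section says "The primary analyses will be aimed at comparing results on the outcome measures at three months after baseline between the MBCT group", with TAU as the other arm and adjustment for baseline levels and other baseline differences. A mixed model appears once, for the 6- and 9-month question, and its stated purpose is to handle repeated measures. No therapy-group or teacher term is named. The Discussion says "To our knowledge, this is the first properly powered randomised controlled study in this field".

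**The concern.** Patients in one MBCT group share a teacher, a room, and exercises in listening and speaking to one another. Their outcomes may be more alike than those of patients in different groups. TAU has no such trial-created grouping, so the design is partially nested, with clustering in one arm.

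With a positive ICC, the variance of the MBCT mean exceeds the value used in the calculation. Two things are then at stake. The first is whether 45 analysed patients per arm give the stated 80% power, and with it the claim to be properly powered. The second is whether a primary test that ignored the groups would hold its 5% type I error.

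**Working it through.** **Inputs from the Sample size section:** difference 4, SD 7.5, pre-post correlation 0.5, two-sided 5%, 80% power, 45 analysed per arm, 25% dropout.

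**Assumptions, not in the article:** m = 8 to 12 analysed patients per group; ICC 0.01 to 0.10 on the baseline-adjusted outcome; total residual variance held at the plan's value; TAU patients independent.

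**1. Reproduce the plan's figure.** Residual SD s = 7.5 × √(1 − 0.5²) = 6.495. Then n per arm = 2 × (1.960 + 0.842)² × 6.495² / 4² = 41.4, so 42. A t-based calculation gives 43. The stated value is approximately 45, and 45 / 0.75 = 60. The dropout allowance accounts for the whole step from 45 to 60, so no design effect is included. Under independence, 45 per arm gives 83% power (normal) or 82% (t).

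**2. Add one-arm clustering.** The design effect in the MBCT arm is DE = 1 + (m − 1) × ICC.

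- SE = s × √((DE + 1)/45).
- Ratio of true to naive SE: r = √((1 + DE)/2).
- Normal power = Φ(4/SE − 1.960).
- Satterthwaite df = (v1 + v2)² / (v1²/(k − 1) + v2²/44), with v1 = DE × s²/45, v2 = s²/45 and k = 45/m groups. Power is then taken from the noncentral t.
- Type I error if groups are ignored ≈ 2 × [1 − Φ(1.988/r)], where 1.988 is the t critical value on 87 df.

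**Example, m = 10, ICC 0.05.** DE = 1.45 and SE = 6.495 × √(2.45/45) = 1.516. Normal power = Φ(2.639 − 1.960) = 75.2%. Satterthwaite df = 9.6, giving 65.9%. r = 1.107, so type I error ≈ 2 × [1 − Φ(1.796)] = 7.3%.

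**3. Results at 45 per arm, in the order m = 8 / 10 / 12.**

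| ICC | Normal power, % | Satterthwaite power, % | Type I error if groups ignored, range over m |
|---|---|---|---|
| 0.01 | 81.9 / 81.5 / 81.2 | 76.9 / 74.7 / 72.2 | 5.1-5.3% |
| 0.02 | 80.6 / 79.9 / 79.2 | 75.2 / 72.4 / 69.2 | 5.5-5.9% |
| 0.05 | 76.9 / 75.2 / 73.5 | 70.4 / 65.9 / 61.0 | 6.7-7.8% |
| 0.10 | 71.0 / 67.9 / 65.0 | 63.2 / 56.8 / 50.1 | 8.7-11.0% |

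Using 1.960 in place of 1.988 gives type I errors of 5.8-6.3%, 7.1-8.3% and 9.2-11.5% at ICC 0.02, 0.05 and 0.10.

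**4. Break-even.** Normal-approximation power stays at 80% while 1 + DE ≤ 45 / (6.495 × 2.802/4)² = 2.174, that is, DE ≤ 1.174. The largest tolerable ICC is 0.174/(m − 1): 0.025 for m = 8, 0.019 for m = 10, 0.016 for m = 12.

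**5. How much is due to few groups.** With 45/12 to 45/8, about 4 to 6 groups, setting DE = 1 in the Satterthwaite formula gives df of 16.7, 13.0 and 10.4 and power of 79%, 77% and 75% for m = 8, 10 and 12. Part of the shortfall is therefore the price of few groups, even with an ICC of zero.

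**The case against.** The analysis half rests on silence. The Primary analyses section writes out no model. It does not even list the centre stratum used in randomisation. The article is condensed, and an analysis plan that is not shown could contain a group effect. This stands. A reader might infer that confidence intervals will be too narrow, but the documents do not support that: it needs both a positive ICC and a final model that omits the group. The sample size basis is different, because it is fixed in the text.

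A reader might also infer that the 80% power is simply not delivered. That does not follow either. At ICC 0.02, normal-approximation power is 79-81%. The dropout assumption may also prove cautious: if all 60 per arm are analysed, power at ICC 0.05 with 8 to 12 per group is 85-88% (normal) or 77-84% (Satterthwaite).

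The assumed group size can be challenged too. If 8 to 12 are allocated per group and 25% are lost, 6 to 9 are analysed. At ICC 0.05 that gives 76-79% (normal) or 68-74% (Satterthwaite), with type I error of 6.1-7.0%. The shortfall is smaller but remains.

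The type I figures need group effects that vary around an average of zero. If MBCT changed no patient's outcome, individual randomisation would leave no group-induced correlation. Lastly, independence in TAU is an assumption: other psychosocial treatments are allowed and their format is not stated.

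These points make the finding conditional. They do not put a clustering allowance into the 45 per arm.

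**Conclusion.** The point holds in conditional form. The calculation treats patients as independent although one arm is taught in groups, and the article gives no reason to expect independence. Rounding up from 42 or 43 to 45 leaves a small reserve. On the normal approximation it covers an ICC of only about 0.016 to 0.025 for groups of 8 to 12.

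Beyond that, the loss at 45 per arm runs from a few percentage points at ICC 0.05 to 9-15 points below 80% at ICC 0.10. A small-sample analysis that respects the groups falls below 80% in every scenario tabulated. All of this rests on an assumed group size and ICC and on the full 25% dropout. The claim to be properly powered should therefore carry that condition.

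**What to change.** 1. Record the MBCT group to which each MBCT patient is assigned.
2. In the 3-month primary analysis, fit a random group effect in the MBCT arm only (each TAU patient a cluster of one), with arm-specific residual variance and Kenward-Roger or Satterthwaite degrees of freedom. Carry the same structure into the repeated-measures model. Specify this before any unblinded analysis.
3. In the Sample size section, state the planned group size and replace the unqualified 80% with power over an ICC range, for example 0.01 to 0.10.

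This does not call for more patients. The documents give no ICC on which to base a larger number, and fewer dropouts than planned would return some power.

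The cost is more than one added sentence and a group identifier. Intervals will be wider, and with only about 4 to 6 groups the group variance is poorly estimated and the few degrees of freedom clearly lower the stated power. At ICC 0.05 that is 61-70% against 74-77% on the normal approximation. The restated power should disclose this.
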